#### Blinding

This clinical trial will be conducted in an assessor-blinded (single-blind) manner. The outcome assessors will remain blinded to group assignments until the completion of the trial, while participants and treating investigators will be aware of the assigned interventions (TBT or TENS). The investigators responsible for outcome assessment will not participate in the randomization process and will not be informed of the group allocation or the type of intervention the participant receives.

The interventions for both the TBT and TENS groups will be performed under standardized procedures and in similar environments to minimize bias. Subject identification codes will be designed to prevent assessors from distinguishing the assigned group. The assignment and management of identification codes will be handled by the study staff and will not be disclosed to the assessors until the trial is complete, except in emergencies where unblinding is necessary for participant safety. All procedures for randomization, allocation, and blinding will be thoroughly documented to ensure transparency and reproducibility.

### Data management and monitoring

Data management and monitoring will be conducted under the study protocol, institutional standard operating procedures (SOPs), Good Clinical Practice (GCP) guidelines, and applicable regulatory requirements. The principal investigator will report AEs and study progress periodically to the sponsor, who will oversee trial conduct through scheduled evaluations.

Monitoring will be conducted by a designated monitor through regular site visits and phone communications to ensure protocol compliance. This includes reviewing original medical records and research documents, as well as consulting with investigators as needed. In this trial, the clinical trial director will initiate monitoring after the enrollment of the first subject and subsequently after every 15 subjects are recruited.

All participant-related documents will use subject identification codes instead of personal names to protect confidentiality. These documents will be securely stored in compliance with data protection regulations. Upon study completion, all research documents will be archived at the trial site for three years following the final study report. Data collected during the trial will be securely stored and managed using an electronic Case Report Form (eCRF) system, ensuring data integrity and confidentiality.

### Statistical analysis

The primary analysis will be performed on the FAS, which will be defined under the ITT principle. In this study, all randomized participants will be analyzed as allocated, except for those who (1) do not meet major inclusion criteria, (2) never receive any intervention specified in the protocol, or (3) have no post-randomization data due to lack of any assessment. The PP set will include participants who complete the study without major protocol violations, such as premature discontinuation of the intervention, violation of inclusion/exclusion criteria, overall intervention compliance below 66.6%, or other significant protocol deviations.

The efficacy of the intervention will be primarily evaluated using the FAS population, with supportive analyses conducted on the PP set. In the event of missing data, the amount and mechanism of missingness will be assessed, and appropriate imputation methods will be selected and applied. All statistical tests will be two-sided, with a significance level of 5%. For all primary and secondary outcomes, point estimates of treatment effects and their corresponding 95% confidence intervals (CIs) will be reported. Effect sizes (e.g., Cohen’s d for continuous variables) will also be presented where appropriate to indicate the magnitude of the observed effects.

Demographic and baseline clinical characteristics will be summarized by treatment group. Continuous variables will be presented as means and standard deviations, and analyzed using Student’s independent t-test or Wilcoxon rank-sum test, depending on normality. Categorical variables will be summarized as frequencies and percentages, and analyzed using Pearson’s chi-squared test or Fisher’s exact test, as appropriate.

All statistical analyses will be performed using Python (version 3.12.4) with its statistical libraries, including statsmodels and scipy. The random assignment will also be conducted using Python (version 3.12.4).

#### Baseline characteristics

Baseline demographic and clinical characteristics of participants will be summarized using descriptive statistics (e.g., mean ± standard deviation for continuous variables, frequencies and percentages for categorical variables). Baseline characteristics will be compared between the two groups to ensure comparability.

#### Primary outcome analysis

The primary outcome, the mean change in TMJ pain VAS from baseline to Week 6 between the TBT and TENS groups, will be analyzed using an Analysis of Covariance (ANCOVA), with the baseline VAS score included as a covariate. The primary analysis will be conducted on an intention-to-treat (ITT) basis, including all randomized participants. In the event of missing values, multiple imputation using chained equations will be employed, assuming data are missing at random (MAR).

#### Secondary outcome analysis

The secondary outcomes include average TMJ pain VAS scores, worst TMJ pain VAS scores, vertical temporomandibular joint opening, including pain-free opening and maximum unassisted opening, JFLS-8 scores, GCPS 2.0 scores, Treatment Expectancy Scale scores, PGIC scores at 0, 6, and 10 weeks. For continuous outcomes measured at multiple time points (e.g., VAS scores at 0, 6, and 10 weeks), linear mixed models will be used to assess within-group and between-group changes over time. Categorical outcomes will be analyzed using chi-square tests.

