### Sample size calculation and statistical hypotheses

The sample size for this trial was determined based on statistical calculations and reference to a previous randomized controlled trial with a similar design [25]. A total of 30 participants (15 in the intervention group and 15 in the control group) will be recruited, considering a 20% dropout rate. This allows for 24 evaluable subjects (12 per group) for the primary analysis.

The hypothesis of this study is as follows:$$\mathrm{H}_o\left(\text{null hypothesis}\right):\mu\mathrm{t}=\mu\mathrm{c}$$$$\mathrm{H}_1\left(\text{alternative hypothesis}\right):\mu\mathrm{t}\neq\mu\mathrm{c}$$

µt denotes the mean change in Visual Analog Scale (VAS, mm) score from baseline to 6 weeks in the experimental group (TBT), and µc is the mean change in VAS (mm) score from baseline to 6 weeks in the control group (TENS). The experimental and control groups will be recruited in a one-to-one ratio.

The calculation assumed a two-sided significance level (α) of 0.05, a type II error (β) of 0.1 (power = 90%), and a 1:1 allocation ratio. A previous RCT with a similar design (10-week intervention, 12 sessions) reported a mean difference of − 2.53 in VAS between groups, with a pooled standard deviation (SD) of 0.96 (Rezaie et al., 2022). For conservative estimation, this study applied a smaller mean difference (–2) and larger SD (1.5).

The required sample size per group was calculated using the formula for a two-sample t-test:

Calculation formula: $$\:\frac{2{({z}_{1-\frac{\alpha\:}{2}}+{z}_{\beta\:})}^{2}\times\:{\sigma\:}^{2}}{\left|{\mu\:}_{T}-{\mu\:}_{c}\right|}=\:\frac{2{(1.96+1.28)}^{2}\times\:{1.5}^{2}}{{(-2)}^{2}}=11.81\approx\:12$$  

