### Outcome measures

#### Primary outcome: visual analog scale

The primary outcome measure is the average temporomandibular joint pain Visual Analog Scale (VAS, 100 mm) score over the past week. It will be assessed at Week 0 (Baseline) and Week 6 (Primary endpoint).

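### The mixed model for continuous secondary outcomes states no baseline adjustment; read plainly, it loses precision and gives a second week-6 average-VAS estimate

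*Protocol article*

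**What the plan says.** In the Protocol article, *Secondary outcome analysis* lists average and worst TMJ pain VAS, the two mouth-opening measures, JFLS-8 and other scales at weeks 0, 6 and 10. For continuous outcomes with several time points, "linear mixed models will be used to assess within-group and between-group changes over time". The example in that sentence is VAS at weeks 0, 6 and 10, so week 0 is one of the modelled times. No baseline adjustment is mentioned.

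*Primary outcome analysis* treats the week-6 change in TMJ pain VAS by ANCOVA, "with the baseline VAS score included as a covariate", with multiple imputation by chained equations for missing values. Average VAS at week 6 therefore appears under both analyses.

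**The concern.** A mixed model over weeks 0, 6 and 10 that targets change is ordinarily fitted with group, time and group-by-time, and with week 0 among the responses. If each arm has its own free baseline mean, the week-6 group-by-time contrast is the difference between arms in mean change. That subtracts the whole baseline difference, where ANCOVA subtracts only the part that baseline predicts.

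Two things are at stake. First, worst pain, mouth opening and JFLS-8 would be compared less precisely than the data allow, in a trial with 12 to 15 participants per arm. Second, the report would hold two numbers for the same week-6 average-VAS effect, with no statement of which one to quote.

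A smaller matter is that within-group change is named beside the between-group comparison. It is not a randomised contrast. Because Table 1 admits only patients with average pain of at least 40 mm, some fall in average VAS is expected in both arms from regression to the mean alone.

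**Working it through.** **Inputs from the document** (*Sample size calculation and statistical hypotheses*): two-sided α 0.05, power 90%, difference 2, SD 1.5, 1:1 allocation, and a total set "considering a 20% dropout rate". The difference and SD appear to be in 0–10 units, although the outcome is scored on 100 mm. The document does not say whether 1.5 is the SD of a score or of a change.

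**Assumed:** ρ, the correlation between baseline and week 6, which is not given and is taken over 0.2 to 0.8; equal SDs at both visits; complete data.

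**The plan's own figure.** n per arm = 2 × (1.96 + 1.28)² × 1.5² / 2² = 2 × 10.4976 × 2.25 / 4 = 11.81, rounded to 12. Then 12 / 0.8 = 15 per arm, 30 in total. The stated size reproduces. It belongs to the primary comparison and nothing below changes it.

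**Variance of the two week-6 contrasts**, with SD σ at each visit and n per arm:
- change-score contrast: (2σ²/n) × 2(1 − ρ)
- baseline-adjusted contrast: (2σ²/n) × (1 − ρ²)
- ratio: 2(1 − ρ) / [(1 − ρ)(1 + ρ)] = 2/(1 + ρ)

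| ρ (assumed) | variance ratio | SE ratio |
|---|---|---|
| 0.2 | 2/1.2 = 1.67 | 1.29 |
| 0.3 | 2/1.3 = 1.54 | 1.24 |
| 0.5 | 2/1.5 = 1.33 | 1.155 |
| 0.7 | 2/1.7 = 1.18 | 1.085 |
| 0.8 | 2/1.8 = 1.11 | 1.05 |

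**Small-sample check by simulation** (20,000 trials per setting, 12 per arm, SD 1.5 at each visit). SE of the change-score contrast against ANCOVA:
- ρ 0.3: 0.724 v 0.595, variance ratio 1.48
- ρ 0.5: 0.611 v 0.540, ratio 1.28
- ρ 0.7: 0.474 v 0.448, ratio 1.12

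The ratios fall slightly short of the formula because ANCOVA must estimate the baseline slope from few participants.

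**How far apart the two week-6 estimates lie.** They differ by (1 − b) times the chance baseline difference between arms, where b is the ANCOVA slope. With b near ρ, the SD of that gap is about (1 − ρ) × 1.5 × √(2/12) = (1 − ρ) × 0.612, or 0.43, 0.31 and 0.18 at ρ 0.3, 0.5 and 0.7. Simulation gave 0.45, 0.33 and 0.21. The gap exceeded 0.5 units, a quarter of the planned difference of 2, in 24%, 12% and 3% of trials. Missing data can widen it, because the primary analysis uses multiple imputation.

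**What drives the loss.** In one simulated dataset (15 per arm, ρ 0.5), the unconstrained group-by-time model gave 0.1826 at week 6, identical to the change-score difference. A mixed model that kept week 0 as a response but gave both arms one baseline mean gave 0.1757, and ANCOVA gave 0.1755. The unconstrained baseline means cause the loss, not the use of week 0 as a response.

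**The case against.** The strongest reply is that the criticised model is not written down. The article gives no fixed effects or covariance structure, and does not say whether baseline means are constrained. Such terms are commonly left to an analysis plan or the full protocol, neither of which is shown. This limits the point but does not remove it. The section does name week 0 as a modelled time and change as the target, while the section before it adjusts for baseline. The plain reading is the less precise model, and a sentence would settle it.

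A reader might infer more than the documents support:

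- **That having week 0 as a response wastes the baseline.** It does not; the common-baseline model recovers the ANCOVA result almost exactly.
- **That the secondary tests will reject too often** because *Statistical analysis* names statsmodels. That section fixes neither a mixed-model routine nor a reference distribution. In a check with 15 per arm and equal correlations between visits, matching the random-intercept model, a normal reference rejected 5.4% of the time under the null, against 4.9% with t degrees of freedom. Larger excesses arose when a random-intercept model was fitted to unequal correlations, a mismatch the plan does not prescribe.
- **That average VAS at week 10 is unscheduled.** The primary-outcome section says "It will be assessed at Week 0 (Baseline) and Week 6 (Primary endpoint", but it covers the primary endpoint only. The Abstract and *Secondary outcome analysis* both give week 10, and the schedule figure is not shown. At most, the wording could be aligned.
- **That efficacy will rest on within-group p-values.** The text speaks of assessing such changes, not testing them. The hypotheses are between-group, and *Statistical analysis* promises treatment-effect estimates with confidence intervals for all primary and secondary outcomes.
- **That it is unclear which week-6 result is primary.** It is the ANCOVA. The second estimate is a reporting matter, and a secondary longitudinal analysis of the same scale is ordinary.

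**Conclusion.** The point holds in a limited form. On the plain reading, the between-group contrasts for continuous secondary outcomes carry 11% to 67% more variance than baseline-adjusted ones for ρ from 0.8 down to 0.2. At ρ 0.3, 0.5 and 0.7 the excess is 54%, 33% and 18%, or 48%, 28% and 12% by simulation at 12 per arm. Average VAS at week 6 also gets a second estimate that can visibly differ from the primary one.

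These sizes rest on an unconstrained group-by-time model, complete data, assumed ρ and equal SDs. With k the ratio of the baseline SD to the week-6 SD, the large-sample ratio is (k² + 1 − 2ρk)/(1 − ρ²). It reaches its minimum of 1 at k = ρ, so the penalty shrinks if baseline varies less than week 6. The 40 mm entry threshold could bring that about for average VAS.

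The choice of primary analysis, the sample size and the conduct of the trial are untouched. The change is worth making because it recovers precision at almost no cost.

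**What to change.** In *Secondary outcome analysis*:

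- For each continuous outcome with a baseline measurement, model weeks 6 and 10 as the responses, with baseline value, baseline-by-time, group, time and group-by-time as fixed effects. Alternatively, keep week 0 as a response and give both arms a common baseline mean.
- Name the between-group difference at week 6 and at week 10, with its confidence interval, as the target. Report within-group change descriptively only.
- State that the week-6 average-VAS effect comes from the ANCOVA in *Primary outcome analysis* alone, and that the mixed model adds week 10 for that scale.
- Optionally, add to the primary-outcome section that average VAS is also recorded at week 10 as a secondary outcome, so that the two sections read alike.

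The cost is a few sentences and a few lines of code. Baseline values are already collected and no new data are needed.

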##### DC/TMD chronic pain grade scale 2.0

This scale comprehensively measures the severity of chronic pain related to temporomandibular disorders, including pain intensity, functional impact, and psychological factors. Grades will be assessed at baseline, week 6, and week 10, and changes over time will be analyzed to determine the effectiveness of pain management.

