##### Patient global impression of change (PGIC)

The PGIC is a 7-point scale used to evaluate the patient’s overall perception of improvement or worsening in health status (1 = very much worse, 7 = very much improved). Changes in PGIC scores at weeks 6 and 10 will be analyzed to assess the subjective effectiveness of the intervention.

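### Chi-square is the only test named for categorical secondary outcomes, yet every candidate is ordered; PGIC is also listed at a week 0 absent from its own definition

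*Protocol article*

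**What the plan says.** All places are in the protocol article.

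- **Secondary outcome analysis** lists average and worst pain VAS, mouth opening, JFLS-8, GCPS 2.0, treatment expectancy and PGIC. The list closes with "PGIC scores at 0, 6, and 10 weeks". Continuous outcomes measured repeatedly go to linear mixed models. For the rest: "Categorical outcomes will be analyzed using chi-square tests". No outcome is named as categorical, and no exact or ordinal method is offered.
- **DC/TMD chronic pain grade scale 2.0**: "Grades will be assessed at baseline, week 6, and week 10". The number of grades is not given.
- **Treatment expectancy scale**: a Likert scale, with 1 to 5 points as the example.
- **Patient global impression of change (PGIC)**: a 7-point scale running from very much worse to very much improved. "Changes in PGIC scores at weeks 6 and 10 will be analyzed to assess the subjective effectiveness of the intervention".
- **Statistical analysis** commits to an effect estimate with a 95% confidence interval for every primary and secondary outcome. It allows Fisher's exact test as an alternative in the paragraph on demographic and baseline variables. **Safety analysis** does the same for adverse events.
- **Sample size calculation and statistical hypotheses**: "A total of 30 participants (15 in the intervention group and 15 in the control group) will be recruited, considering a 20% dropout rate". After that loss the plan counts on 12 per arm, 24 in all.

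**The concern.** VAS, mouth opening in mm and the JFLS-8 total are continuous. That leaves GCPS grade, treatment expectancy and PGIC as the possible categorical outcomes, and all three are ordered. A Pearson chi-square test gives the same result however the categories are arranged, so it spends its degrees of freedom on every pattern of difference and not on a shift towards better ratings. With 24 to 30 people spread over several levels, its large-sample approximation is also weak. A comparison at a single visit would disregard the baseline grade, although the GCPS section speaks of change over time.

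Separately, PGIC already rates change. A value at week 0 has nothing to refer to, and the phrase about changes in PGIC does not say whether it means the rating at each visit or a difference between visits.

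At stake are secondary results on chronic pain grade and patient-rated change, which the Discussion counts among the strengths of the design.

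**Working it through.** **1. The plan's own figure.** With two-sided alpha 0.05, 90% power, difference 2 and SD 1.5: 2 × (1.96 + 1.28)² × 1.5² / 2² = 11.81, so 12 per arm. With 20% dropout: 24 / (1 − 0.2) = 30. The stated size reproduces. It concerns the primary VAS only; no power is stated for GCPS or PGIC.

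**2. Expected counts.** With equal arms, the expected count in a cell is half its category total. Reaching 5 therefore needs 10 people in that category. At N = 30 at most 30/10 = 3 categories can do so; at N = 24 at most 2 (24/10 = 2.4). The average expected count with 15 per arm is 15/7 = 2.1 for seven levels and 15/5 = 3 for five.

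**3. Simulation.** Pearson chi-square on the 2 × k table (empty categories dropped) was set against the tie-corrected Wilcoxon rank-sum test, with 4,000 trials per scenario. The documents give no category distributions or effect sizes for these outcomes, so the following are assumptions.

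- PGIC, 7 levels, control shares: 2/5/13/30/28/16/6% or 1/3/6/25/35/22/8%.
- GCPS, control shares: 5 grades at 5/25/40/20/10%, or 4 grades at 30/40/20/10%.
- Effect: a common odds ratio of 4, 6 or 8; odds ratio 1 for type I error. On a latent logistic scale, ln(OR)/1.814 gives shifts of 0.76, 0.99 and 1.15 SD. The plan's primary effect is 2/1.5 = 1.33 SD.

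| Outcome | Per arm | Chi-square power | Rank-sum power |
|---|---|---|---|
| PGIC, 7 levels | 12 | 0.16–0.43 | 0.43–0.75 |
| PGIC, 7 levels | 15 | 0.21–0.58 | 0.51–0.85 |
| GCPS, 4–5 grades | 12 | 0.21–0.55 | 0.40–0.75 |
| GCPS, 4–5 grades | 15 | 0.30–0.68 | 0.50–0.84 |

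- Scenario by scenario, chi-square kept 37 to 68% of the rank test's power for PGIC (a loss of 32 to 63%) and 51 to 81% for GCPS (a loss of 19 to 49%).
- Type I error at odds ratio 1: chi-square 0.025–0.027 for PGIC and 0.031–0.045 for GCPS; rank-sum 0.043–0.046.
- Cells with an expected count below 5, among non-empty categories: 82–98% for PGIC and 67–94% for GCPS. The usual limit of 20% of cells below 5 was exceeded in at least 99.9% of trials.

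**4. A second set of assumptions.** Five grades, control shares 10/25/30/20/15%, 6,000 trials per setting. With 15 per arm, a latent shift of 0.8 SD gave 25% (chi-square) against about 50% (rank-sum), a loss of about 50%. A shift of 1.33 SD gave 67% against 90%, a loss of 1 − 67/90 = 26%. With 12 per arm the figures were 19% against 41% (loss 54%) and 54% against 82% (loss 34%).

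**5. PGIC timing.** The analysis section gives weeks 0, 6 and 10. The outcome definition gives weeks 6 and 10. The schedule figure is not available to settle it.

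**The case against.** The sentence on categorical outcomes names none. The same section calls GCPS and PGIC scores and lists them beside VAS and JFLS-8, so they might be meant for the mixed model. The article also condenses a fuller protocol, said to be a supplementary file, where outcomes could be matched to tests. Both points stand, and they rule out saying that chi-square is prescribed for GCPS and PGIC. They do not clear the text. If these outcomes belong in the mixed model, the chi-square sentence covers nothing on the list, grades are treated as continuous, and PGIC enters with a week-0 value. The section fixes a method; it is not merely silent.

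A reader might go further in three ways that the documents do not support.

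- *The tests are invalid.* Sparse cells suggest this, but the simulated error never exceeded 5%. The test is conservative.
- *Half the power is lost.* That is about right for a 7-level PGIC in some scenarios. Most GCPS scenarios lose less, and every figure depends on assumed distributions. Nor is chi-square blind to a shift; it detects one less often.
- *PGIC is scheduled at week 0.* The only basis is a phrase closing a long list of outcomes. The definition gives weeks 6 and 10, and its wording on changes can be read as the ratings at those visits or the difference between them, both computable.

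It is also fair to say that proportional-odds regression with a baseline covariate may meet sparse cells or separation with 24 to 30 people.

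**Conclusion.** The concern holds in limited form. Chi-square is the only test given for categorical secondary outcomes, the only candidates are ordered, and the section does not say which of them it means. If applied to them, it costs roughly 20 to 50% of a rank test's power for a 4- or 5-grade GCPS (54% in one further scenario) and roughly 30 to 65% for a 7-level PGIC. These ranges rest on the assumed shares, on proportional-odds or latent shifts of 0.76 to 1.33 SD, and on an assumed number of GCPS grades. Chi-square would also leave the promised estimates and intervals undelivered. It would not inflate false positives.

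The week-0 entry for PGIC contradicts the outcome definition and needs reconciling, but it leaves the week 6 and 10 comparisons and their power untouched. The primary VAS analysis is a separate ANCOVA and is unaffected. Severity is minor.

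**What to change.** In Secondary outcome analysis:

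- State for each listed outcome whether it is continuous, ordered, or nominal/binary.
- For ordered outcomes, replace chi-square with a Wilcoxon rank-sum test, tie-corrected or by permutation, or with proportional-odds regression. For GCPS, adjust for baseline grade where the model can be fitted with 24 to 30 people, and name the rank test as the fallback.
- Report an effect with its 95% confidence interval: a common odds ratio, or the probability that a TBT participant has the better rating than a TENS participant.
- Analyse the PGIC rating itself at weeks 6 and 10, delete week 0 for PGIC, and reword the reference to changes in PGIC scores in its definition.
- Use Fisher's exact test for any binary or nominal outcome.

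The cost is wording and a little programming. No data collection or sample size changes. The exact option of the rank-sum routine in scipy makes no tie correction, so heavily tied ratings need the tie-corrected approximation or a permutation version. The choice should be recorded before outcomes are compared by group.
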